### **8.2.2 Vital Signs**

Oral, tympanic or rectal temperature (keeping the same methodology throughout the study, if possible), pulse rate, respiratory rate, and blood pressure will be assessed before blood collection for laboratory tests.

Blood pressure and pulse measurements will be assessed in a supine position with a completely automated device. Manual techniques will be used only if an automated device is not available.

Blood pressure and pulse measurements should be preceded by at least 5 minutes of rest for the subject in a quiet setting without distractions (e.g., television, cell phones). Pulse will be measured once. Blood pressure will be measured with 2 consecutive readings recorded at intervals of at least 1 minute. The average of the 2 blood pressure readings will be recorded on the CRF.

### **8.2.3 Electrocardiograms**

Single 12-lead ECG will be obtained as outlined in the SoA (Table 1-1 for Part 1 and Table 1-2 for Part 2) using an ECG machine that automatically calculates the heart rate and measures PR, QRS and QT intervals.

### **8.2.4 Clinical Safety Laboratory Assessments**

Safety laboratory tests listed in Table 8-1 will be performed by the local laboratory at the timepoints as outlined in the SoA (Table 1-1 for Part 1 and Table 1-2 for Part 2). Additional tests may be performed at any time during the study as determined necessary by the Investigator or required by local regulations.

**Table 8–1 Protocol-Required Safety Laboratory Assessments**

| Laboratory Assessments | Parameters                                                                                                                                                                                                                                                                                 |
|-------------------------------|---------------------------------------------------------------------------------------------------------------------------------------------------------------------------------------------------------------------------------------------------------------------------------------------------|
| Haematology                   | White cell blood count with differential count, including absolute neutrophil count a and lymphocyte count a
Red blood cell count and haemoglobin
Platelet count                                                                                                      |
| Clinical Chemistry            | Sodium, potassium, chloride, calcium, phosphate
ALT, AST, ALP, total or direct bilirubin
Total protein, albumin
Serum creatinine
CRP a and LDH a
For Part 2 - additionally a :
Ferritin
cTnT or cTnI (choice dependent on local laboratory) |
| Coagulation                   | Prothrombin time and activated partial thromboplastin time
D-dimers a and fibrinogen a                                                                                                                                                                                   |
| Other screening tests         | Estimated creatinine clearance according to Cockcroft-Gault formula                                                                                                                                                                                                                               |

ALP = alkaline phosphatase; ALT=alanine aminotransferase; AST = aspartate aminotransferase; CRP = C-reactive protein; LDH = lactate dehydrogenase.

a. Measured as disease biomarkers (see Section 8.8)

The results of protocol-required safety laboratory assessments should be recorded in the CRF. In addition, the Investigator must review the laboratory report, document this review, and record any clinically relevant changes occurring during the study in the AE section of the CRF. The laboratory reports must be filed with the source documents. Clinically relevant abnormal laboratory findings are those which are not associated with the underlying disease, unless judged by the Investigator to be more severe than expected for the subject's condition.

All laboratory tests with values considered clinically abnormal during the 28-day FU period should be repeated until the values return to normal or baseline or are no longer considered clinically significant by the Investigator or Medical Monitor.

- If such values do not return to normal/baseline within a period of time judged reasonable by the Investigator, the aetiology should be identified, where possible, and the Sponsor notified.
- All protocol-required laboratory assessments, as defined in Table 8–1, must be conducted in accordance with the laboratory manual and the SoA.
- If laboratory values from laboratory assessments not specified in the protocol and performed at the institution's local laboratory result in the need for a change in subject management or

are considered clinically relevant by the Investigator (e.g., are considered to be an SAE or an AE or require dose modification), then the results must be recorded in the CRF.

### **8.3 Adverse Events and Serious Adverse Events**

The definitions of AEs and SAEs can be found in Appendix 4.

AEs will be reported by the subject (or, when appropriate, by a caregiver, surrogate, or the subject's legally authorised representative).

The Investigator and any qualified designees are responsible for detecting, documenting, and reporting events that meet the definition of an AE or SAE and remain responsible for following up AE that are serious, considered related to the study treatment or the study, or that caused the subject to discontinue the study (see Section 7).

#### **8.3.1 Time Period and Frequency for Collecting AE and SAE Information**

All AEs and SAEs will be collected from the signing of ICF to the EOS visit at the timepoints specified in the SoA (Table 1-1 for Part 1 and Table 1-2 for Part 2).

All SAEs will be recorded and reported to the Sponsor or designee within 24 hours, as indicated in Appendix 4. The Investigator will submit any updated SAE data to the Sponsor within 24 hours of it being available.

Investigators are not obliged to actively seek AEs or SAEs after the conclusion of study participation. However, if the Investigator learns of any SAE, including death, at any time after a subject has been discharged from the study, and he/she considers the event to be reasonably related to the study treatment or study participation, the Investigator must promptly notify the Medical Monitor (or the Sponsor after study closure).

#### **8.3.2 Method of Detecting AEs and SAEs**

The method of recording, evaluating, and assessing causality of AEs and SAEs and the procedures for completing and transmitting SAE reports are provided in Appendix 4.

Care will be taken not to introduce bias when detecting AEs and/or SAEs. Open-ended and non-leading verbal questioning of the subject is the preferred method to inquire about AE occurrence.

### **8.3.3 Follow-up of AEs and SAEs**

After the initial AE/SAE report, the Investigator is required to proactively follow each subject at subsequent visits/contacts. All SAEs, and non-serious AEs of special interest (as defined in Section 8.3.6), will be followed until resolution, stabilisation, until the event is otherwise explained, or the subject is lost to follow-up (as defined in Section 7.3). Further information on follow-up procedures is given in Appendix 4.

### **8.3.4 Regulatory Reporting Requirements for SAE**

Prompt notification (within 24 hours, see Appendix 4) by the Investigator to the Sponsor of an SAE is essential so that legal obligations and ethical responsibilities towards the safety of subjects and the safety of a study treatment under clinical investigation are met.

The Sponsor has a legal responsibility to notify both the local regulatory authority and other regulatory agencies about the safety of a study treatment under clinical investigation. The Sponsor will comply with country-specific regulatory requirements relating to safety reporting to the regulatory authority, IRB/IEC, and Investigators.

An Investigator who receives an Investigator safety report describing an SAE or other specific safety information (e.g., summary or listing of SAE) from the Sponsor will file it along with the Investigator's Brochure and will notify the IRB/IEC, if appropriate according to local requirements.

### **8.3.5 Pregnancy**

- Details of all pregnancies in female subjects and, if indicated, female partners of male subjects will be collected after the study treatment and until the EOS.
- If a pregnancy is reported, the Investigator should inform the Sponsor within 24 hours of learning of the pregnancy and should follow the procedures outlined in Appendix 5, to collect information and determine the pregnancy outcome.
- Abnormal pregnancy outcomes (e.g., spontaneous abortion, foetal death, stillbirth, congenital anomalies, ectopic pregnancy) are considered to be SAEs.

### **8.3.6 Adverse Events of Special Interest**

Adverse events of special interest include infusion related reactions (including hypersensitivity or anaphylaxis during or within 24 hours of XVR011 infusion and hypersensitivity reactions (other than IRR) and will be reported using the same process as for AEs).

All subjects should be closely observed under medical supervision during the XVR011 infusion administration and for  $\geq 120$  minutes thereafter. Vital signs, including blood pressure, heart and respiratory rates and body temperature will be evaluated for possible hypersensitivity reactions. Any type of ECG will be performed if a subject experiences cardiac symptom.

Emergency equipment, such as adrenaline, antihistamines, corticosteroids, and respiratory support (inhalational therapy, oxygen, and artificial ventilator) must be available. Medication for infusion reactions (IRR) should be available for immediate use.

As with any protein, infusion reactions (IRR)/hypersensitivity reactions may occur. This may vary from mild to moderate signs and symptoms but may also be a severe or life-threatening anaphylactic/anaphylactoid reaction. Signs and symptoms may include hypotension, tachycardia, bronchospasm, dyspnoea, oedema/angio-oedema, dizziness, headache, nausea, abdominal pain, fever, rash. Guidance in case of an infusion reaction based on severity of the reaction provided in Table 8–2.

**Table 8–2                      Guidance in case of an infusion reaction based on severity of the reaction**

| Infusion reaction   | Study treatment actions                                                                                                                                                                                                                                                    | Other treatment (see also institutional standard practice for infusion reactions)                                                             |
|----------------------------|-----------------------------------------------------------------------------------------------------------------------------------------------------------------------------------------------------------------------------------------------------------------------------------|------------------------------------------------------------------------------------------------------------------------------------------------------|
| Grade 1 - mild             | Reduce rate of infusion                                                                                                                                                                                                                                                           | Consider symptomatic treatment                                                                                                                       |
| Grade 2 - moderate         | Interrupt infusion
Restart infusion if signs/symptoms have responded well to symptomatic treatment
Infusion should be restarted at a slower rate:
If symptoms worsen or recur, permanently stop infusion
If symptoms do not worsen or do not recur, continue infusion | Administer symptomatic treatment e.g. antihistamines, NSAIDs wait for signs/symptoms to improve before re-starting infusion                          |
| Grade 3 - severe           | Permanently stop infusion                                                                                                                                                                                                                                                         | Administer antihistamines, corticosteroids, bronchodilators, IV fluids, vasopressors and other treatments as per Investigator judgement              |
| Grade 4 – life-threatening | Permanently stop infusion                                                                                                                                                                                                                                                         | Administer antihistamines, corticosteroids, bronchodilators, IV fluids, vasopressors and other life support treatments as per Investigator judgement |

Abbreviation: NSAID = nonsteroidal anti-inflammatory drugs.

The medical staff has to be trained in resuscitation and immediate intensive care has to be easily accessible in case of severe life-threatening events.

## **8.4 Treatment of Overdose**

For this study, any dose of XVR011 greater than the intended dose (i.e., dose level 1, dose level 2 or dose level 3 depending on cohort and study part) within a 24-hour time period will be considered an overdose.

The Sponsor does not recommend specific treatment for an overdose.

In the event of an overdose, the Investigator should:

- 1 Contact the Medical Monitor immediately.
- 2 Closely monitor the subject for AE/SAE and laboratory abnormalities until the EOS.
- 3 Provide appropriate treatment as per the clinical judgement of the Investigator for any such AE/SAE.
- 4 Obtain plasma samples for PK analysis as per SoA.
- 5 Document the quantity of the excess dose as well as the duration of the overdosing in the CRF.

## **8.5 Pharmacokinetics**

Serum samples of approximately 1 mL will be collected for measurement of serum concentrations of XVR011 as specified in the SoA. The timing of sampling may be altered during the course of the study based on newly available data (e.g., to obtain data closer to the time of peak plasma concentrations) to ensure appropriate monitoring. Instructions for the collection and handling of biological samples will be provided in a separate laboratory manual. The actual date and time (24-hour clock time) of each sample will be recorded.

Samples will be used to evaluate the PK of XVR011 and processed as described in the laboratory manual. Genetic analyses will not be performed on these samples. Subject confidentiality will be maintained.

During Part 2, drug concentration information that would unblind the study will not be reported to investigative sites or blinded personnel until the study has been unblinded.

Any changes in the timing of timepoints for any planned study assessments must be documented and approved by the relevant study team member and then archived in the Sponsor and site study files but will not constitute a protocol amendment. The IRB/IEC will be informed of any safety issues that require alteration of the safety monitoring scheme or amendment of the ICF.

Samples may be stored for a maximum of 5 years following the last subject's last visit for the study at a facility selected by the Sponsor to enable further analysis of immune responses to XVR011.

## **8.6 Pharmacodynamics**

For the assessment of viral load in nasopharyngeal refer to Section 8.1.3.

For biomarkers refer to Section 8.8.

## 8.7 Genetics

Genetics are not evaluated in this study.

## 8.8 Biomarkers

Blood samples for biomarker research are required and will be collected from all subjects in this study as specified in the SoA (Table 1-1 for Part 1 and Table 1–2 for Part 2). The following disease biomarkers will be analysed by a local laboratory at the site along with clinical safety laboratory parameters (see Table 8–1):

- C-reactive protein (CRP)
- Lactate dehydrogenase (LDH)
- D-dimers
- Fibrinogen
- Absolute neutrophil count
- Lymphocyte count
- Part 2: additionally, ferritin and cardiac troponin T or I

Two additional samples will be collected at Day 1 and Day 3 and stored for a maximum of 3 years following the last subject's last visit for the study at a facility selected by the Sponsor to enable further analysis of biomarker responses to XVR011. These samples are only collected for subjects who provide specific consent for this. The blood volume required to be collected will be outlined in the informed consent and laboratory handling instructions.

Samples will be tested to evaluate the effect of XVR011 on the disease biomarkers in subjects hospitalised for COVID-19.

## 8.9 Immunogenicity Assessments

Antibodies to XVR011 will be evaluated in serum samples collected from all subjects, according to the SoA.

Serum samples will be screened for antibodies binding to XVR011 and the titre of confirmed positive samples will be reported. Other analyses may be performed to verify the stability of antibodies to XVR011 and/or further characterise the immunogenicity of XVR011.

The detection and characterisation of antibodies to XVR011 will be performed using a validated assay method by or under the supervision of the Sponsor. Additional samples may be collected to

further characterised and/or evaluated antibodies for their ability to neutralise the activity of the study treatment. For more details see laboratory manual.

Instructions for the collection and handling of biological samples will be provided in a separate laboratory manual.

Samples may be stored for a maximum of 3 years following the last subject's last visit for the study at a facility selected by the Sponsor to enable further analysis of immune responses to XVR011.

## **8.10 Medical Resource Utilisation and Health Economics**

Health Economics/Medical Resource Utilisation and Health Economics parameters are not evaluated in this study.

## 9 Statistical Considerations

### 9.1 Statistical Hypotheses

**Part 1:** No formal hypothesis is postulated for Part 1.

**Part 2:** In Part 2, capacity of XVR011 in reducing time to recovery (sustained) as compared to placebo will be tested in a superiority setting. The primary endpoint will be tested using the stratified log-rank test. It is assumed that the placebo and active cumulative survival curves for TTR do not follow an exponential distribution. Moreover, the HR cannot be assumed as constant during the 28-day FU period.

### 9.2 Sample Size Determination

**Part 1:** There is no formal sample size calculation for Part 1. Considering the target of XVR011 is a viral protein and the absence of any binding with human proteins in preclinical studies, 9 subjects per cohort are considered adequate as an initial assessment of the safety of a single dose of XVR011 in this population.

**Part 2:** The sample size for the Phase 2 part of the study is based on the primary endpoint, time to recovery defined as reaching level 1 to 3 of the 8-point scale within 28-day FU period and which is maintained at or below level 3 for the subsequent, consecutive 14 days; a 2:1 randomisation with a one-sided alpha of 0.025, 80% power and allowing for a 15% drop-out rate. The sample size required to test the primary endpoint is obtained by comparing with the log-rank test, the piecewise exponential cumulative survivals described in Table 9–1 and is 408 subjects allowing 275 events to be observed. A total of 408 subjects will be randomised, 272 to the XVR011 arm and 136 to the placebo arm.

**Table 9–1**                      **Determination of Sample Size with Different Time to Recovery Assumptions for Placebo and XVR011 Treatment**

|               | Placebo Cumulative
“Survival”* | XVR011 Cumulative
“Survival”* | HR   |
|---------------|-----------------------------------|----------------------------------|------|
| Day 1  | 100%                              | 100%                             |      |
| Day 5  | 80%                               | 50%                              | 3.11 |
| Day 7  | 50%                               | 25%                              | 1.47 |
| Day 29 | 20%                               | 20%                              | 0.24 |

\* “Survival” refers to absence of recovery

Note: Sample size scenarios: Primary endpoint time to recovery, 2:1 randomisation, 1-sided alpha = 0.025 and power 80%.

### 9.3 Populations for Analyses

For purposes of analysis, the following analysis sets are defined:

**Table 9–2 Populations for Analysis**

| Population (Analysis Set)               | Description                                                                                                                                                                                                                                                                                                                                                                                     |
|------------------------------------------------|--------------------------------------------------------------------------------------------------------------------------------------------------------------------------------------------------------------------------------------------------------------------------------------------------------------------------------------------------------------------------------------------------------|
| Enrolled Analysis Set (EAS)                    | All subjects who signed the ICF (including screening failures).                                                                                                                                                                                                                                                                                                                                        |
| Full Analysis Set (FAS)                        | The FAS is defined under an intent-to-treat population principle.
Part 1: The FAS comprises all subjects to whom study treatment has been dispensed.
Part 2: The FAS comprises all subjects to whom study treatment has been randomised. Statistical analyses will be based on study treatment groups as per randomisation, irrespective of the study treatment actually received. |
| Per Protocol Analysis Set (PPS), if applicable | Part 1: The PPS comprises all the FAS subjects who received study treatment.
Part 2: The PPS comprises all the FAS subjects who received study treatment and have a positive RT-PCR test at baseline (central laboratory). In both Part 1 and Part 2, a subject will be completely excluded from the PPS in case of protocol deviations affecting study analyses.                     |
| Safety Analysis Set (SAF)                      | The safety analysis set consists of all subjects who started infusion with study treatment. Subjects will be analysed according to the study treatment they actually received. A precise definition of “as actually received” will be added in the statistical analysis plan (SAP).                                                                                                                    |
| PK Analysis Set (PKS)                          | The PK analysis set consists of all subjects in the safety analysis set with at least one drug concentration value.                                                                                                                                                                                                                                                                                    |

EAS = enrolled analysis set; FAS = full analysis set; ICF = informed consent form; PK = pharmacokinetics; PPS = per protocol analysis set.

In SAF, safety data of subjects will be listed and summarised under the treatment actually received independently of total amount of the treatment received. As an example, a subject who was randomised into the control arm (placebo) but received EXVR011 by mistake, will be considered as:

- a placebo-treated subject in the FAS and PPS
- an EXVR011 treated subject in the SAF

The FAS will be the primary analysis set for all efficacy analyses and the PPS will be used to demonstrate robustness of results for the primary efficacy endpoints.

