#### Type of Subject and Disease Characteristics

3. Has ongoing SARS-CoV-2 infection confirmed by positive RT-PCR test and/or positive antigen test  $\leq 72$  hours of randomisation\*. If the positive test result is older than 72 hours, a positive re-test (RT-PCR or antigen) during screening is required.
4. If dyspnoea and/or tachypnoea are present, an onset of at most 3 days prior to randomisation\* is allowed.
5. Requires medical care in hospital for COVID-19 (i.e., level 4 or 5 of the 8-point ordinal scale).

*\*For Part 1 randomisation means IWRS treatment registration.*

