### **8.1.3 Viral Load**

The antiviral activity of study treatments will be assessed by measuring the nasopharyngeal viral loads.

Nasopharyngeal swabs will be collected at the timepoints specified in the SoA (Table 1-1 for Part 1 and Table 1–2 for Part 2). Samples will be tested for the presence of SARS-CoV-2 using the SARS-CoV-2 RT-qPCR assay. Virologic assessments will include quantitative measures of viral RNA and will be conducted by a central laboratory. At baseline and on Day 8, the genotype of the SARS-CoV-2 virus will be determined.

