### 9.4.3 Secondary Efficacy Endpoints

Proportion of subjects who are alive and do not require any form of mechanical ventilation at Day 8. Proportion of subjects requiring non-invasive or invasive, mechanical ventilation, proportion of subjects requiring intensive care unit (ICU) transfer, and all-cause mortality rate within 28-day FU period will be presented.

Total duration (days) of oxygen supplementation within 28-day FU period, change from baseline in the nasopharyngeal viral load (RT-qPCR) will be reported as continuous endpoints.

Proportion of subjects with clinical status evolving to each level of the 8-point ordinal scale at Days 2, 3, 4, 8, 15, 22, and Day 29, compared to baseline, will be tabulated in a shift table.

Time to event secondary endpoints will be analysed using a methodology similar to the analysis of the primary efficacy endpoint.

In Part 1, the secondary endpoints will be summarised descriptively.

In Part 2, the comparison between XVR011 and placebo will be conducted for every secondary endpoint and resulting p-values will be presented.

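### The main Part 2 viral load comparison includes randomised subjects with no virus on the central baseline swab, which shrinks the estimated antiviral difference by their share

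*Protocol*

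**What the plan says.** - **Endpoint.** Change from baseline in RT-qPCR viral load is the only endpoint listed for the Part 2 antiviral objective (Table 3–2). Section 9.4.3 says that "change from baseline in the nasopharyngeal viral load (RT-qPCR) will be reported as continuous endpoints", and that in Part 2 "the comparison between XVR011 and placebo will be conducted for every secondary endpoint and resulting p-values will be presented".
- **Analysis set.** Under Table 9–2, Section 9.3 says: "The FAS will be the primary analysis set for all efficacy analyses and the PPS will be used to demonstrate robustness of results for the" (the sentence ends by naming the primary efficacy endpoints). For Part 2, "The FAS comprises all subjects to whom study treatment has been randomised"; there is no virological condition.
- **Entry test.** Inclusion criterion 3 reads "Has ongoing SARS-CoV-2 infection confirmed by positive RT-PCR test and/or positive antigen test", dated within 72 hours of randomisation or repeated at screening. It does not call for the central laboratory.
- **Viral load measurement.** Table 1–2 schedules a separate nasopharyngeal swab on Day 1 before dosing. Section 8.1.3 adds: "Virologic assessments will include quantitative measures of viral RNA and will be conducted by a central laboratory".
- **Per-protocol set, Part 2.** "The PPS comprises all the FAS subjects who received study treatment and have a positive RT-PCR test at baseline (central laboratory"). The Part 1 definition has no such condition.
- **Subgroups.** Section 4.2 names baseline viral load level as a subgroup factor.

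**The concern.** A subject can qualify on an antigen or RT-PCR test up to 72 hours before randomisation, start the infusion up to 12 hours after it, and have no detectable virus on the central swab in between. That subject starts at the assay floor, so no decline can be measured on either arm. The protocol has a baseline-positive set, but assigns it to time to sustained recovery, a clinical endpoint that can be measured without baseline virus. It does not assign it to viral load change, which cannot.

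At stake is the reading of the antiviral objective. The FAS estimate would understate the fall produced in subjects who had virus to clear, and its p-value could miss a real effect if the test ignores baseline.

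**Working it through.** The protocol states no power, SD or effect size for viral load, so there is no figure of its own to reproduce.

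**Inputs from the protocol:** 272 on XVR011 and 136 on placebo (Section 9.2); two-sided 5% tests (Section 9.4.1).

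**Assumptions, none in the protocol:** share negative at baseline p; true difference among positives d = 0.5 log10; SD of change among positives s = 1.5 log10; mean fall among positives m = 2 log10 on placebo, hence 2.5 on XVR011; negatives scored as zero change. Dropout is ignored.

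**Step 1, dilution.** Expected FAS difference = (1−p)·d + p·0 = (1−p)·d. With p = 10%, 20%, 30% this is 0.45, 0.40, 0.35 log10. The factor (1−p) does not depend on d, s or m. It depends only on the negatives showing no change.

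**Step 2, unadjusted FAS.** Variance in an arm = (1−p)s² + p(1−p)m², using that arm's own mean fall. For p = 10%:
- XVR011: 0.9 × 2.25 + 0.09 × 6.25 = 2.5875
- Placebo: 0.9 × 2.25 + 0.09 × 4 = 2.385
- SE = √(2.5875/272 + 2.385/136) = 0.1645
- z = 0.45/0.1645 = 2.736; power = Φ(2.736 − 1.960) = 78%

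**Step 3, baseline-quantifiable subjects only.** n = 244.8 and 122.4; SE = √(2.25/244.8 + 2.25/122.4) = 0.1661; z = 0.5/0.1661 = 3.011; power = 85%.

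**Step 4, FAS adjusted for baseline status.** The term p(1−p)m² drops out (a small term remains because the effect differs between positives and negatives). SE ≈ √(0.9 × 2.25 × (1/272 + 1/136)) = 0.1494; z = 0.45/0.1494 = 3.011, the same as in Step 3. Power returns to about 85%, but the estimate is still 0.45.

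| Share negative | FAS difference (log10) | FAS power, unadjusted | Quantifiable-only power |
|---|---|---|---|
| 5% | 0.475 | 84% | 87% |
| 10% | 0.45 | 78% | 85% |
| 20% | 0.40 | 66% | 81% |
| 30% | 0.35 | 55% | 76% |

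With a placebo fall of 3 log10, unadjusted FAS power at 10%, 20% and 30% negative is 71%, 54% and 41%.

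**Check by simulation.** With p = 10%, s = 1.5, m = 2 and d set to 0.465 (80% power in positives only), power was 72% for the unadjusted FAS, 79% for the FAS adjusted for baseline-negative status, and 79% for positives only. The mean estimated differences were 0.417, 0.416 and 0.461. Adjustment restored the power but not the size of the estimate.

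**The case against.** **The power loss is not fixed by the protocol.** Section 9.4.3 names no model or covariate for viral load, and further detail is left to the SAP, which is not shown. A reader might infer that the choice of the FAS in itself costs power. The documents do not support that: Step 4 shows that the loss comes from omitting baseline adjustment, and the protocol does not say that adjustment will be omitted. This objection stands in full.

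**Zero change is an assumption.** Section 9.4.1 says that missing data are not imputed unless stated otherwise, and nothing says what value a not-detected baseline takes. If it takes none, no change can be computed and the subject drops out of this analysis. This stands as a condition on the finding. It also means that the population actually analysed would depend on a coding choice.

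**Baseline-negatives may be few.** Entry requires a recent positive test, and any dyspnoea or tachypnoea must have begun at most 3 days before randomisation. A reader might take the per-protocol condition as evidence that negatives are common. It shows only that they are foreseen, and the 20% and 30% rows have no support in the text. The assumed fall is also not tied to a visit; a smaller early fall would narrow the power gap.

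**All-randomised analysis is conventional, and the baseline viral load subgroup helps.** Both are true. The FAS estimate is a legitimate average over everyone randomised, and the preference for another set is partly a choice of estimand. But the subgroup does not change the main estimate or its p-value, and an average that includes subjects in whom the measurement cannot fall is a weak measure of antiviral activity.

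**Conclusion.** The point holds as a matter of analysis population. Section 9.3 settles the set for every efficacy endpoint, so a SAP that made a baseline-quantifiable set the main one for viral load would depart from the protocol as written. Under the plan, the antiviral estimate is diluted by exactly the share of baseline-negatives, provided that they are scored as no change.

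A loss of power is conditional on an unadjusted test: 78% against 85% at 10% negative, under the assumptions listed. A reader might instead compare 78% with the 89% that would apply if nobody were negative (0.5/0.1575 = 3.174; Φ(3.174 − 1.960) = 89%). That overstates the case, because restriction recovers only to 85%. The endpoint is secondary and carries no stated power, so this is an inexpensive improvement and not a threat to the trial's main conclusion.

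**What to change.** In Sections 9.3 and 9.4.3, state that the main Part 2 analysis of change in viral load compares the arms as randomised, in subjects with a quantifiable central RT-qPCR result on the Day 1 pre-dose swab, with baseline log10 viral load as covariate. Keep the FAS analysis as a sensitivity analysis. Quantifiable is somewhat stricter than the positive result used for the per-protocol set, but it is what a change score needs.

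The selection uses only a pre-dose value, so treatment cannot influence it and the randomised comparison is preserved. The swab and the central assay are already scheduled. The cost is a sentence or two of text, fewer subjects (about 367 of 408 if 10% are negative, 408 × 0.9) and a narrower population for this one secondary endpoint.
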